## Abstract

**Introduction:**

Though evidence has revealed the beneficial effects of cognitive improvement interventions on breastfeeding, the effect of psychological interventions has rarely been studied. This study aims to test whether promoting a positive emotion intervention, ‘Three Good Things’ intervention, during the last trimester of pregnancy can enhance early colostrum secretion and breastfeeding behaviours by modulating the hormones associated with lactation (prolactin and insulin-like growth factor I). We will attempt to promote exclusive breastfeeding by using physiological behavioural measures.

**Methods and analysis:**

This study is designed as a randomised controlled trial conducted in the Women’s Hospital School of Medicine at Zhejiang University and the Wuyi First People’s Hospital. The participants will be randomly divided into two groups using stratified random grouping: the intervention group will receive ‘Three Good Things’ intervention, while the control group will write about three things that come to mind first. These interventions will be continued from enrolment until the day of delivery. Maternal blood hormone levels will be tested approaching delivery and the following day after birth. Behavioural information about breastfeeding will be collected 1 week afterwards.

**Ethics and dissemination:**

The study has been approved by the Ethics Committees of the Women’s Hospital School of Medicine at Zhejiang University and the Wuyi First People’s Hospital. Results will be disseminated through peer-reviewed journals or international academic conferences.

**Trial registration number:**

ChiCTR2000038849.

Strengths and limitations of this studyA randomised controlled trial of pregnant women will be performed to evaluate the effect of ‘Three Good Things’ on their postpartum emotions, colostrum secretion and breastfeeding behaviours.‘Three Good Things’ is a typical psychological intervention used for promoting positive emotions, which has shown significant effects.‘Three Good Things’ is feasible to carry out by individuals and easy to disseminate in daily routines.We will promote breastfeeding-related behaviours in the postpartum hospitalisation period in the setting of a Baby-Friendly hospital, in line with future trends in China.The result interpretations on breastfeeding behaviours are limited in postpartum period due to the limits of existing conditions.

## Introduction

Breastfeeding is one of the most valid ways for promoting children’s health and survival, which is advocated by the WHO and the United Nations Children’s Fund (UNICEF).^1^ Breast milk, with its balanced nutrition, suitable temperature and economic benefits, is considered the most ideal natural food for infants.^2 3^ In addition, breast milk contains a diverse array of microbiota and myriad biologically active components that contribute to the development of infants’ immune systems. Thus, compared with formula-fed infants, breastfed children have fewer incidences of disease and lower mortality rates.^4 5^ Breastfeeding also has economic benefits for individual families as well as at the national level by improving child development and reducing health costs.^6^ As the WHO suggests, infants should be exclusively breastfed (given nothing else but breastmilk) for the first 6 months of life and be allowed to breastfeed to 2 years of age or longer.^7^ In 2012, the 56th World Health Assembly set a goal for 2025 to increase exclusive breastfeeding rates in the first 6 months to at least 50%. However, few countries in the world fully meet the recommended standards, according to a recent report by UNICEF and the WHO in collaboration with the Global Breastfeeding Collective, a new initiative to increase global breastfeeding rates.^8^ The *Global Breastfeeding Scorecard*, which evaluated 194 nations, found that only about 40% of children are breastfed exclusively within the first 6 months of life, and only 23 countries exceed the standard of 60% on their exclusive breastfeeding rates.^8^

To promote exclusive breastfeeding in the first 6 months postpartum, a large number of studies have explored the influencing factors and intervention measures. A previous study indicated that a positive antenatal attitude towards breastfeeding was the strongest predictor and was associated with a 20%–30% increase in breastfeeding initiation and maintenance at all time points.^9^ Accordingly, the Breastfeeding Support Programme was carried out to improve the attitudes and cognitions about breastfeeding among pregnant women. It was found to be an effective measure to delay the cessation of breastfeeding, increasing both its duration and its exclusivity.^10^

In addition to cognitive factors, psychological status and emotions also play an important part in breastfeeding. Current evidence suggests that anxiety and depression are associated with lower exclusive breastfeeding behaviours.^11–13^ Psychological distress resulted in low appetite, weight loss and poor nutritional status, all of which made it difficult to breastfeed.^14^ Emotional and traumatic stressors were found to have the greatest impact on breastfeeding outcomes.^15^ Of clinical relevance, addressing prenatal and postpartum distress as a part of the implementation of breastfeeding practice interventions could improve breastfeeding rates.^16^ Although intervention studies have been focusing on psychological distress, few studies have conducted positive psychology interventions (PPIs) to promote breastfeeding. PPIs can enhance women’s mental well-being during the perinatal period.^17^ Thus, PPIs may be worth exploring as measures to promote breastfeeding behaviours.^18^ The ‘Three Good Things’, as a PPI instructs participants to write down three good things every night, was proposed by Seligman *et al* in 2005. It helps to develop skills in regulating emotions,^19^ which can enhance the experience of positive emotions and alleviate the symptoms of depression.^20^ This psychological intervention has been tested in multiple studies and is replicable and easy to implement by individuals. Therefore, this study will use and evaluate the effect of ‘Three Good Things’ as an intervention to enhance positive emotions and reduce negative emotions among pregnant women.

Breastfeeding behaviours are influenced by lactation capacity, which is reflected in hormone levels. Prolactin (PRL) is a protein hormone secreted by the anterior pituitary gland that can stimulate and maintain lactation. Insulin-like growth factor I (IGF-I) is a kind of polypeptide that can mediate the galactagogue of growth hormone. Previous studies have shown that emotions and the secretion of these two hormones are closely related. Positive emotions can promote the secretion of prolactin, while depression can lead to a prolactin secretion imbalance and stress events and anxiety can also lead to a low secretion level of IGF-I.^21–23^ This study aims to use ‘Three Good Things’ intervention to promote positive emotions among pregnant women during mid-pregnancy and late pregnancy, thus improving the secretion of lactation-related hormones and the initiation and continuation of breastfeeding behaviours.

## Methods and analysis

### Aims

The study is designed as a randomised controlled trial (RCT) in China, to test whether the ‘Three Good Things’ intervention during late pregnancy can enhance colostrum secretion and related breastfeeding behaviours and effects. We also aim to examine whether the association between prenatal emotions and postnatal breastfeeding behaviours are mediated by lactation-related hormones.

### Hypotheses

Hypothesis 1a: ‘Three Good Things’ interventions can promote the secretion of PRL and IGF-I by enhancing positive emotions and reducing negative emotions in pregnant women.

Hypothesis 1b: ‘Three Good Things’ interventions can improve maternal breastfeeding willingness and postpartum in-hospital breastfeeding behaviours by enhancing positive emotions and reducing negative emotions.

Hypothesis 2a: Increased secretion of PRL and IGF-I will predict the promotion of breastfeeding behaviours and effects.

Hypothesis 2b: Positive emotions can indirectly promote breastfeeding behaviours during postpartum hospitalisation through the secretion of PRL and IGF-I, while negative emotions have adverse effects.

### Study design

This is the protocol for a randomised controlled clinical trial. Between October 2020 and June 2021, a pilot study was carried out at the First People’s Hospital of Wuyi County in Zhejiang Province. During this time, a total of 96 pregnant women were recruited for the test of the designed survey questionnaire, including the baseline survey and follow-up survey and intervention questionnaire. In January 2022, the formal trial was conducted at Women’s Hospital School of Medicine at Zhejiang University. This study will have three phases: T_0_, baseline; T_1_, immediate postintervention and T_2_, follow-up (1 week after delivery). The qualitative and quantitative data will be collected in three phases. T_1_ is a baseline survey collecting demographic information, data about existing positive and negative emotions and their intention to breastfeed. T_2_ is the intervention process for the intervention and the control groups, with process variables of emotion and willingness collected every week. T_3_ is the prenatal and postnatal hospitalisation period when we will collect outcome indicators such as serum hormone levels, positive and negative emotions, intention to breastfeed, breastfeeding behaviour and other indicators. Figure 1 illustrates the overall study design.

**Figure 1 F1:**
[figure not shown]
Flow chart of the breastfeeding intervention project. The participants will be randomly divided into intervention group and control group. In phase T_0_, participants will complete the first questionnaire, including breastfeed intention, emotional scale and writing practice persistence. In the T_1_ stage, the participants will complete a series of intervention questionnaires, including breastfeed intention, emotional scale and writing practice persistence. First lactation hormone test will be performed before delivery. The second lactation hormone test will be performed after delivery. Finally, a postpartum questionnaire will be performed about the outcome of lactation behaviour.

### Recruitment

The study will be conducted in the Women’s Hospital School of Medicine at Zhejiang University. We will include primiparous pregnant women at 34–38 gestational weeks. The exclusion criteria are as follows:

Women with no intention to give birth in a designated hospital.Women not giving birth for the first time.Women with a disease that prevents breastfeeding (cardiac insufficiency, infectious diseases, neurological or cognitive damage, etc)Pregnant women with more than one fetus.

### Sample size

Based on the results of the pilot study, statistical power (1−β) of 80%, and a two-tailed significance level (α) of 0.05, we calculated the targeted sample size with a two-sample t-test allowing unequal variance. Given the breastfeeding behaviour score (LATCH) was 12.72 in the intervention group (SD=2.33) and 12.06 in the control group (SD=1.51), the theoretical sample size was shown as N1=N2 = 141. Considering a dropout rate of 20%, the ultimate sample size needed was estimated at 353 individuals.

### Randomisation and blinding

Medical staff at the hospital’s fetal heart monitoring studio will help recruit participants. We will use stratified random grouping to divide the pregnant women into two groups according to the level of support they say they receive (high, average and none) from family members in the oral interview. Baseline data will be collected before the randomisation. Pregnant women received on the same day will be randomly assigned to the intervention group and the control group according to the level of support (high, average and none). [name] will generate the randomisation list, and YX will carry out the randomisation and give the participants information about which group they are allocated to. Our trial will be a single-blinded trial of participants.

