### Intervention

At the fetal heart monitoring studio, we will ask the participants to add our Wechat account, and the subsequent communications and relevant questionnaire distribution will be carried out through Wechat chat software. In the T_1_ stage, participants will complete a series of intervention questionnaires. Participants in the intervention group will be asked to write down three good things that have happened during the day every 2 days, with weekly specific themes. Participants in the control group will only have to write about three things that come to mind first that are related to the same theme. To improve the compliance and interest of the participants, we will set up different instructions and themes for them weekly (table 1). Meanwhile, if a participant forgets to write, we will send out hints if they fail to complete the questionnaires. When the participant is unwilling to take the initiative to fill in the questionnaire, we will ask for reasons and send encouraging messages (eg, about the benefits of participating in the project). For ethical considerations of avoiding excessive disturbance, the participants will be regarded as loss-to-follow-up, after three non-responses.

**Table 1 T1:** Instructions for the intervention and control groups

Week	Topic	Instructions for the intervention group	Instructions for the control group
1	My baby	Please recall three good things that happened to you today related to you and your baby, and record them with the reasons why they happened. Here are some examples: My baby is moving today, and my baby is growing healthily. I saw a cute baby picture today, and my baby may be cuter. I bought baby’s little clothes today, they are so small and cute.	Please record the first three baby-related events that come to your mind today, and record them and the reasons why they happened. Here are some examples: I suddenly thought that it is not easy to have a child. I had the maternity check-up today.

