### Evaluation and outcomes

Primary outcomes will include exclusive breastfeeding and on-demand feeding during postnatal hospitalisation. Exclusive breastfeeding means that the baby is not given any liquid or solid food other than breast milk. This indicator will be included in the postnatal questionnaire and also be double-checked in the hospital care records of formula. On-demand feeding means breastfeeding according to the baby’s needs. Since the infant’s early urination reflects breastfeeding, changing diapers 6–8 times a day in the early postpartum period is considered feeding on demand.

Secondary outcome indicators will mainly include other breastfeeding behaviours during postpartum hospitalisation (first postnatal food for babies is breast milk; LATCH breastfeeding score), lactation-related hormone secretion (prolactin and IGF-I) and postpartum breastfeeding intention and postpartum emotion.

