### Data collection and follow-up

On the day of enrolment, pregnant women will be asked to complete an enrolment questionnaire providing information about general demographic characteristics and other factors influencing breastfeeding. Meanwhile, if the enrolment questionnaire finds prenatal depression among the participants, we will refer them to the department of psychology. Then, the ecological instantaneous evaluation of both groups will be performed every week to determine the trend of change in intention and emotions until delivery. The measurement of emotion uses the Positive and Negative Affect Scale (PANAS) and 10 positive items for positive emotions proposed by Fredrickson for validation.^24 25^ Postpartum questionnaires on breastfeeding behaviour during postnatal hospitalisation will be completed 1 week after delivery. Blood samples will be collected twice, after they are admitted to the hospital approaching delivery and after delivery at 7 to 8 am (vaginal delivery: the morning after one night; caesarean section: the morning after two nights), and evaluated for prolactin and IGF-I to evaluate postpartum lactation ability. The blood draw will be conducted by nurses in the ward.

On recruitment, general demographic variables will be collected: education, occupation, number of permanent household members, total average annual household income and expected date of birth. Other influencing factors will include mode of delivery, self-reported ease of breastfeeding, degree of sleep disturbance, self-reported importance of early exclusive breastfeeding, knowledge of breastfeeding, birth injury and nipple cracking pain scores, degree of hospital support, depression (measured by Edinburgh Postnatal Depression Scale, EPDS), anxiety (measured by Generalised Anxiety Disorder, GAD-7), breastfeeding intentions (measured by Infant Feeding Intentions Scale, IFI), breastfeeding behaviour score (LATCH), resilience (Brief Resilience Scale, BRS) and potential number of traumatic events.^26–31^ Generally, Baby-Friendly hospitals will take measures such as early sucking and skin-to-skin contact within 1 hour after delivery, limitation of bottle used, room-in, etc.^32^ We will also record and report routine measures taken in this Baby-Friendly hospital.

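### The protocol says women are told their group and also that they are blinded; read literally, the single-blind claim fails for the participant-reported outcomes

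*Protocol article*

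**What the plan says.** The Randomisation and blinding section assigns one person to generate the list and another to carry out the randomisation. The second person will also "give the participants information about which group they are allocated to". The sentence that follows reads: "Our trial will be a single-blinded trial of participants".

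The Intervention section describes a writing task in both arms. The intervention arm records three good things every 2 days on a weekly theme. For the comparator, "Participants in the control group will only have to write about three things that come to mind first that are related to the same theme". Table 1 gives the weekly instructions for each arm, and those for the intervention arm ask for good things every week.

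Evaluation and outcomes names two primary outcomes, exclusive breastfeeding and on-demand feeding during the postnatal stay. On exclusive breastfeeding it says: "This indicator will be included in the postnatal questionnaire and also be double-checked in the hospital care records of formula". On-demand feeding is inferred from diaper counts: "changing diapers 6–8 times a day in the early postpartum period is considered feeding on demand". Under Data collection and follow-up, "Postpartum questionnaires on breastfeeding behaviour during postnatal hospitalisation will be completed 1 week after delivery". Emotion (by PANAS and a set of positive items) and breastfeeding intention are followed weekly until delivery, with questionnaires distributed through WeChat. Prolactin and IGF-I are measured in two blood samples.

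**The concern.** A participant cannot be told her allocation and be blinded to it. The two statements are adjacent, and both describe what will be done, so this is not a detail that a fuller document would merely add. Staff who follow the first sentence defeat the second.

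A comparator that also writes on the same theme can help to separate a specific effect of positive writing from expectancy, but only while women do not know which task is the one under test. A woman who knows that she is in the promoted arm of a breastfeeding study may rate her mood, her intention or her feeding more favourably. On an outcome that rests on her answer alone, that shift cannot be told apart from an effect of the intervention. Emotion is also the first link in hypotheses 1a, 1b and 2b, so a reporting shift there would carry into the exploratory mediation analysis.

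**Working it through.** **Step 1. The two statements.** One has group membership conveyed to the participant. The other has the participant as the blinded party. They are compatible only if what is conveyed does not reveal which arm is active, for example a neutral label or the woman's own instructions alone. The article does not say that in this section, under Intervention, or in the Figure 1 legend.

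**Step 2. Which outcomes are exposed.**
- Emotion and breastfeeding intention: participant-reported on scales, with no external check. Exposed.
- On-demand feeding (primary): based on diaper counts. The instrument described for feeding behaviour is the 1-week questionnaire, and no record check is stated. Exposed.
- Exclusive breastfeeding (primary): questionnaire plus formula records. Partly protected. The definition excludes any liquid or solid other than breast milk, while the named record concerns formula.
- Prolactin and IGF-I (secondary): blood assays. Not exposed to reporting bias.
- LATCH (secondary): the article does not say who scores it, so I leave it unclassified.

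**Step 3. The plan's own sample size.** Inputs from the Sample size section are "statistical power (1−β) of 80%, and a two-tailed significance level (α) of 0.05", LATCH means 12.72 and 12.06, and SDs 2.33 and 1.51. The difference is 0.66 and the sum of variances is 2.33² + 1.51² = 7.709. With the unequal-variance t-test, power is 0.7999 at 140 per arm and 0.8027 at 141, so 141 per arm is reproduced. Then 282 / (1 − 0.20) = 352.5, which gives 353. The blinding point does not depend on this figure; 141 is borrowed below only as a number per arm, and it was derived for LATCH, not for a binary outcome.

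**Step 4. A hypothetical for scale.** None of these assumptions comes from the documents: true exclusive breastfeeding is 50% in both arms; a fraction m of intervention mothers who did not breastfeed exclusively report that they did; control mothers never misreport; the formula record corrects nothing.

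Bias b = m × 0.50. SE = √(2 × 0.25 / 141) = 0.0595. Type I error = Φ(−1.96 + b/SE) + Φ(−1.96 − b/SE).

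| m | b (points) | b/SE | Type I error |
|---|---|---|---|
| 5% | 2.5 | 0.42 | 7.0% |
| 10% | 5.0 | 0.84 | 13.4% |
| 15% | 7.5 | 1.26 | 24.2% |

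**Step 5. How the hypothetical moves.** If the record caught half of the false reports at m = 10%, the bias would be 5.0 × 0.5 = 2.5 points and type I error would return to about 7.0%. If control mothers misreported at 5% against 10%, the net bias would be 5.0 − 2.5 = 2.5 points, with about the same result. With equal misreporting in both arms, the bias is zero and type I error stays at 5%.

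**The case against.** The strongest reply is that every woman has to be given arm-specific writing instructions, so something must be conveyed at allocation. On that reading women learn their task but not which task is active, and the single-blind sentence is true. A condensed article may also leave the allocation script to the full protocol. This reading is possible, and it rules out asserting that blinding has in fact failed. It does not remove the defect: the sentence speaks of group allocation, not of the task, and nothing in the article limits what is disclosed.

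Other points stand in full:
- The article gives no masking rationale for the control task, and it states the 2-day frequency only for the intervention arm. That the comparator was built for blinding, or matched in frequency, is inference.
- Both arms write within the same study, and the encouraging messages about the project's benefits are not confined to one arm. Over-reporting common to both arms would largely cancel; only the differential part biases the comparison.
- The formula-record check guards the very outcome used in the hypothetical.
- A neutral task name cannot mask fully, because the intervention instructions themselves ask for good things.
- Consent pages are not in the copy reviewed, so what women are told about the hypothesis cannot be judged.

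**Conclusion.** The contradiction is real and should be corrected. As written, the procedure tells participants their group, so the stated single-blind property does not hold. The consequence is confined to outcomes that rest on the participant's own report: emotion, intention and on-demand feeding, with exclusive breastfeeding exposed only in part.

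A reader might infer more: that blinding has certainly been lost, that every outcome is compromised, or that the trial's type I error is 7% to 24%. The documents support none of these. The allocation sentence may be loosely worded; the hormone assays are not open to reporting bias, and the formula record offers partial corroboration; and the type I figures rest on an assumed 50% rate, misreporting in one arm only, and no correction from the record. They show that modest differential misreporting would matter on an unchecked binary outcome of this size. They are not an estimate for this trial.

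**What to change.** Reword the allocation step so that each woman receives only her own writing instructions, under one neutral task name used in both arms. Withhold the arm label (intervention or control) until after the 1-week questionnaire, subject to ethics committee agreement. State in the protocol what is disclosed and what is withheld, and acknowledge that masking will be partial.

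State also that the hospital formula record decides exclusive breastfeeding during the stay when it disagrees with the questionnaire. Because the record covers formula, a mother's report of some other fluid is not contradicted by a record that shows no formula.

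If group disclosure is to stay, delete the single-blind claim, describe the trial as open-label to participants, and interpret the self-reported outcomes accordingly.

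The cost is a change to the allocation script and protocol wording, with ethics committee review where information is withheld, and a debriefing after the 1-week questionnaire. No change to sample size or visits is needed. For women already allocated under the present wording, report what they were told.
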